**________________________________________________________**

### Principal Investigator: [name] [name], Lecturer (Occupational Therapy), PDUNIPPD

1. **Title:** Task-based and Magnified Mirror Therapy for Unilateral Spatial Neglect among Post-Stroke Subjects: A Randomized Controlled Trial
2. **Summary:**

Background: Up to 90% of the post-stroke survivors may experience the Unilateral Spatial Neglect (USN). USN is a deficit of attention and is described as the inability to report, respond, or orient to sensory or visual stimuli when it appears on the side opposite to the lesion. USN affects motor recovery, functional performance, and quality of life.

Novelty: The proposed study would be the first investigation to utilize the task-based and magnified mirror therapy for both upper and lower limbs and visual feedback by positioning mirror in parasagital position.

Objective: The primary objective is to determine the effectiveness of Task-based and magnified mirror therapy on Unilateral Spatial Neglect (USN) as well as motor recovery among post-stroke hemiparetic subjects.

Methods:

Design: Randomized controlled, single blinded trial

Setting**:** Neuro-Rehab Laboratory

Inclusion criteria: Age: 20 to 80 years, ischemic or hemorrhagic stroke, 1 to 36 months post-stroke, hemiparesis (right or left), USN (an asymmetry between the Letter cancellation task).

Exclusion Criteria: Severe other cognitive impairment, homonymous hemianopia, contractures and deformities of hand / finger, Severe depression.

Sample size: 86

Intervention: Experimental group will receive 40 sessions, 5/week, during 2 months, 1 hour experimental intervention in addition to 1 hour conventional rehabilitation. Experimental intervention will comprise of task-based and magnified mirror therapy for both upper and lower limbs in addition to the visual feedback. Control group will receive dose matched standard rehabilitation only.

Outcome measure: Letter cancellation task, Line bisection test, Fugl-meyer assessment, Catherine Bergego scale, Functional ambulation category, Berg balance scale, Modified Rankin scale.

Data analysis: A repeated-measures 2-way ANOVA will be used to study difference for the post intervention (8-week) and follow-up (4-week) scores between the groups.

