**Hypothesis:**

1. Task-based and Magnified Mirror therapy protocol for the paretic upper limb provided for 2 months will decrease the Unilateral spatial neglect by 50% in 1 to 36 months post stroke subjects with hemiparesis when compared with the conventional management.
2. Task-based and Magnified Mirror therapy protocol for the paretic upper limb provided for 2 months will enhance the motor recovery by 30% in 1 to 36 months post stroke subjects with hemiparesis when compared with the conventional management.

**Design***:* Randomized controlled, single blinded trial

**Setting:** Neuro-Rehab Laboratory*,* Department of Occupational Therapy, Pt. Deendayal Upadhyaya National Institute for Persons with Physical Disabilities, New Delhi

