**Data Analysis:**

The data will be analyzed by using IBM SPSS version 23.0. The demographic and baseline features of the study participants will be analyzed in form of mean (SD) / median (IQR) / n (%) and appropriate test [(Mann-Whitney U (U) / independent t (t) / chi-square (χ^2^)] tests will be used to analyze the difference for the characteristics between the groups. For inferential statistics, an intention-to-treat analysis method will be used by carrying forward the last observation. A repeated-measures 2-way ANOVA (continuous data; within factor, time; between factor, group) will be used to study difference for the post intervention and follow-up scores between the groups. The pre-intervention score will be considered as the covariate with group as the independent variable and posttest score as the dependent variable. The significance level will be set at *P*<.05. The dummy tables to represent the findings are provided below -

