|  | Language impairment (writing/reading) - *n (%)* |  |  | χ^2^:p = |

BPL: Below poverty line, LIG: Lower income group, MIG: Middle income group, HIG: Higher income group, UG: Under graduate, PG: Post graduate, BRS-U: Brunnstrom recovery stage of arm, BRS- H: Brunnstrom recovery stage of hand, BRS- L: Brunnstrom recovery stage of lower limb SD: Standard deviation , MAS- Modified ashworth scale, IQR – Inter quartile range, AFO-Ankle foot orthosis, VAS – Visual analog Scale

**Table 2: Changes in Pre- and Post-intervention, and Follow-up scores of the Letter Cancellation Task (LCT) between the experimental and control groups**

| **Outcome measure** | **Pre-intervention** | | **Post-intervention (8-week)** | | **Follow-up (12-week)** | |  | | |
| --- | --- | --- | --- | --- | --- | --- | --- | --- | --- |
|  | **Experimental Group (n=43)** | **Control Group (n=43)** | **Experimental Group (n=43)** | **Control**  **Group (n=43)** | **Experimental Group (n=43)** | **Control**  **Group (n=43)** | **Difference between the means**  **(95% CI)** | **F** | **P value** |
| **LCT (Right)**  *Mean*±*SD*  *Maximum score = 20* |  |  |  |  |  |  |  |  |  |
| **LCT (Left)**  *Mean*±*SD*  *Maximum score = 20* |  |  |  |  |  |  |  |  |  |

n – Number, SD – standard deviation, CI - confidence interval, F – test value ANOVA

**Table 3: Changes in Pre- and Post-intervention, and Follow-up scores of the Line Bisection Test (LBT) between the experimental and control groups**

| **Outcome measure** | **Pre-intervention** | | **Post-intervention (8-week)** | | **Follow-up (12-week)** | |  | | |
| --- | --- | --- | --- | --- | --- | --- | --- | --- | --- |
|  | **Experimental Group (n=43)** | **Control Group (n=43)** | **Experimental Group (n=43)** | **Control**  **Group (n=43)** | **Experimental Group (n=43)** | **Control**  **Group (n=43)** | **Difference between the means**  **(95% CI)** | **F** | **P value** |
| **LBT (Right)**  *Mean*±*SD*  *Maximum score = 20* |  |  |  |  |  |  |  |  |  |

n – Number, SD – standard deviation, CI - confidence interval, F – test value ANOVA

**Table 4: Changes in Pre- and Post-intervention, and Follow-up scores of the Fugl-Meyer Assessment (FMA) between the experimental and control groups**

| **Outcome measure** | **Pre-intervention** | | **Post-intervention (8-week)** | | **Follow-up (12-week)** | |  | | |
| --- | --- | --- | --- | --- | --- | --- | --- | --- | --- |

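### Two analysis models are named without being reconciled, and Tables 2–6 give one result per row across three visits, so the 8-week effect is not identified as the test

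*Protocol*

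**What the plan says.** The Data Analysis section describes the analysis of the continuous outcomes in two consecutive sentences. The first, which compares the two arms, reads "A repeated-measures 2-way ANOVA (continuous data; within factor, time; between factor, group) will be used to study difference for the post intervention and follow-up". The second is "The pre-intervention score will be considered as the covariate with group as the independent variable and posttest score as the dependent variable". The second has a single post-test response and no time factor. Nothing says how it relates to the first.

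The Summary has only the first model and no covariate: "A repeated-measures 2-way ANOVA will be used to study difference for the post intervention (8-week) and follow-up (4-week) scores between the groups".

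Dummy Tables 2–6 (LCT, LBT, FMA, CBS, BBS) have columns for pre-intervention, week 8 and week 12 in each group. They end with one "Difference between the means" column (with 95% CI), one F and one P value per row. The footnotes identify F only as the ANOVA statistic. Tables 7 and 8 (FAC, mRS) differ: they have a separate chi-square test at each visit.

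The Hypothesis section says that the therapy "provided for 2 months will decrease the Unilateral spatial neglect by 50% in 1 to 36 months post stroke subjects with hemiparesis" and "provided for 2 months will enhance the motor recovery by 30% in 1 to 36 months post stroke subjects with hemiparesis", each against conventional management. This gives a treatment duration and implies the 8-week assessment (T2), but names no visit.

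**The concern.** Three things stay open: whether time has two levels or three, which effect fills the F and P columns (group, group-by-time, or a contrast at one visit), and which visit answers the hypotheses. The candidate analyses estimate different quantities, so the same data could give different effect sizes and P values for LBT, LCT and FMA, the primary measures. If the choice is made after the data are seen, the primary result depends on it.

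A single averaged result also merges two questions: whether the therapy works by the end of treatment, and whether the effect lasts four weeks longer.

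**Working it through.** **The plan's own figure.** Box 1 gives mean difference 8.6, SD 10.6, α 0.05 and β 0.1, and states 37 per group. For a two-sided comparison of two means, n = 2 × [10.6 × (1.960 + 1.282) / 8.6]² = 31.9, so 32 per group, or 33 with the t distribution. The stated 37 is not reproduced. It equals 32 × 1.15 = 36.8 rounded up, so a dropout allowance may already be in it. It exceeds what its inputs need, so power is not harmed. For the present point, what matters is that these inputs describe a single comparison of two means and name no visit.

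**Inputs for the comparison.** From the documents: difference 8.6, SD 10.6, 37 per group, two-sided α taken as 0.05, visits at baseline, week 8 and week 12. Assumed, not in the documents: no group difference at baseline, SD 10.6 at every visit, compound symmetry with within-subject correlation r from 0.3 to 0.7, and a true 8-week difference of 8.6. The 12-week difference is set to 8.6 (sustained), 4.3 (half) or 0 (lost).

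**What each reading estimates.**

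| Reading | Formula | Sustained | Half | Lost |
|---|---|---|---|---|
| Week-8 ANCOVA | d8 | 8.6 | 8.6 | 8.6 |
| Group effect, weeks 8 and 12, baseline as covariate | (d8 + d12)/2 | 8.6 | 6.45 | 4.3 |
| Group effect, three visits | (0 + d8 + d12)/3 | 5.73 | 4.30 | 2.87 |
| Group-by-time, weeks 8 and 12 | d8 − d12 | 0 | 4.3 | 8.6 |
| Group-by-time, three visits | 2 df | no single difference | no single difference | no single difference |

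**SD of the analysed quantity** (per patient):

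- Week-8 ANCOVA: 10.6 × √(1 − r²), which is 10.11, 9.18 and 7.57 at r = 0.3, 0.5 and 0.7.
- Two-visit group effect: 10.6 × √[(1 + r)/2 − r²], which is 7.93, 7.50 and 6.36.
- Three-visit group effect: 10.6 × √[(1 + 2r)/3], which is 7.74, 8.65 and 9.48.

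**Power at 37 per group**, from the noncentral F with noncentrality n × estimate² / (2 × SD²):

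| Reading | r = 0.3 | r = 0.5 | r = 0.7 |
|---|---|---|---|
| Week-8 ANCOVA, any scenario | 0.95 | 0.98 | 1.00 |
| Two-visit group effect, sustained | 1.00 | 1.00 | 1.00 |
| Two-visit group effect, lost | 0.63 | 0.68 | 0.82 |
| Three-visit group effect, sustained | 0.88 | 0.80 | 0.73 |
| Three-visit group effect, lost | 0.35 | 0.29 | 0.25 |

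The three-visit interaction has power 0.86, 0.96 and 1.00 (sustained or lost), but cannot fill a column that asks for one difference and its CI. The two-visit interaction rejects at 5% when the effect is fully sustained.

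**Price of a week-8 contrast.** Take an effect of half an SD, 43 per group, r = 0.6, sustained. Week-8 ANCOVA: 0.5 / √(1 − 0.36) = 0.625 SD, power 0.82. Two-visit average: 0.5 / √(0.8 − 0.36) = 0.754 SD, power 0.93.

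**The case against.** The strongest reply is that the two sentences form one coherent model. The full ANOVA sentence, like the Summary, compares post-intervention and follow-up scores, so the time levels named are weeks 8 and 12. The next sentence enters baseline as covariate. No analysis sentence makes baseline a level of time, and the pre-intervention columns in Tables 2–6 may be purely descriptive. Averaging two post-treatment visits is a legitimate choice, and with a sustained effect it loses neither effect size nor power. The tables also show means by group at each visit, so persistence can be inspected. Covariance structure and similar details may be left to an SAP.

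Most of this stands. The repeated-measures ANCOVA is the reading closest to the text, and the three-visit group effect is less well supported. But the covariate sentence has a single post-test score, the Summary has no covariate, and the table shells do not say which effect or visit their one result refers to. These are conflicts inside the protocol, not detail left for later. Even the coherent reading yields an average that equals the 8-week effect only if week 12 shows the same difference. Visit means by group do not supply a pre-specified week-8 test.

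Stronger readings are tempting but unsupported:

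- A reader might infer that the 8-week effect is not tested at all. The covariate sentence alone, with the post-test taken at week 8, is an ANCOVA of exactly that effect.
- A reader might infer that the sample size was built on an end-of-treatment contrast. The Sample size section and Box 1 name no visit, and the Literature review describes the source trial's result at 6 months.
- A reader might extend the point to every outcome. FAC and mRS in Tables 7 and 8 are tested visit by visit.

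**Conclusion.** The point holds as a failure to identify the test. The protocol names two models without reconciling them, and Tables 2–6 provide for one result across three visits, so nothing fixes the 8-week effect as what the reported difference, F and P refer to.

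For a true 8-week difference of 8.6, the reading closest to the text reports anything from 8.6 (sustained at week 12) down to 4.3 (lost by then). If baseline is treated as a time level, which the three-visit tables allow, the report is 5.7 down to 2.9. Power at 37 per group on that reading is then 0.88 to 0.73 even with a sustained effect, as r rises from 0.3 to 0.7, against 0.95 to 1.00 for an 8-week ANCOVA.

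The power figures rest on equal SDs, compound symmetry and the assumed correlations, none of which is in the documents. The averaging of the estimates needs only the assumed visit differences. The loss of one third belongs to the less supported reading and should not be taken as the expected consequence of the plan.

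**What to change.** State one model for the continuous outcomes in both the Data Analysis section and the Summary: 8- and 12-week scores as the response, baseline score as covariate, and group, visit and group-by-visit terms. Name the adjusted group difference at 8 weeks as the primary contrast and the 12-week difference as secondary. In Tables 2–6, replace the single difference, F and P columns with one adjusted difference, 95% CI and P value per visit, and keep the pre-intervention columns as description.

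The cost is wording and table shells; no visit, measurement or patient is added. The statistical price is some power relative to the two-visit average if the effect is sustained: 0.82 against 0.93 in the half-SD example above. In return, the primary estimate no longer depends on what happens after treatment ends.

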USN is a strong predictor of poor motor recovery and functional performances among the stroke subjects.[^12^](#_ENREF_12) The impaired ability has significant physical, social, and emotional implications. Considering the International Classification of Functioning, Disability and Health, USN undoubtedly affects body structure and function that subsequently leads to activity limitation and participation restriction.

Cognitive rehabilitation has been recommended as one of the important areas of stroke research that warrant independent synthesis of evidence generated in LMICs.[^13^](#_ENREF_13) Further, globally, research on cognitive impairment after stroke is at an earlier stage of evolution than research in motor recovery.[^14^](#_ENREF_14) The studies to enhance cognitive deficits among stroke survivor are recommended as a top first question for research.[^15^](#_ENREF_15) The proposed study may be applicable to the *National Stroke Registry Program (NSRP) / National Programme for Prevention and Control of Cancer, Diabetes, Cardiovascular Diseases and Stroke* (NPCDCS) in terms of rehabilitation services to control and prevent disability for comprehensive management of stroke patients.[^16^](#_ENREF_16)^,^ [^17^](#_ENREF_17)

[^15^](#_ENREF_15)

1. **Literature review:**

USN is a frequent and disabling impairment after stroke. The terms unilateral neglect, visuospatial neglect, hemineglect and spatial neglect are used interchangeably. Although the USN usually occurs on the contralesional side in the right brain damage, the deficit may be observed on the ipsilesional side as well as among subjects with the left brain damage.[^11^](#_ENREF_11)^,^ [^18^](#_ENREF_18)^,^ [^19^](#_ENREF_19) The functional performance of an individual with USN gets hampered. Most of the investigations have been focused on the impairment and management of upper limb functions. In addition to this, the USN affects lower limb functions such as locomotion and stair climbing. The post-stroke subjects with USN are at more risk of falling in comparison to the subjects without USN.[^20^](#_ENREF_20)^,^ [^21^](#_ENREF_21) The functional ambulation including stair climbing gets more impaired than the stroke subjects without USN.[^20^](#_ENREF_20)^,^ [^22^](#_ENREF_22) Further, USN has been identified as a key element that may impede upper limb and lower limb recovery.[^12^](#_ENREF_12)

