***Rationale:*** Cognitive deficits are a major cause of disability in post- stroke subjects. Spatial neglect has visual, perceptual, and motor factors. Post-stroke with USN exhibited poor functional outcome when compared with individuals without USN. The presence of USN is associated with poor upper limb motor control, both at subacute and chronic stages.[^12^](#_ENREF_12) A range of therapeutic approaches comprising cognitive and behavioral approaches has been applied in visuospatial neglect. However, there is no consensus as to which rehabilitation method is most effective.[^23^](#_ENREF_23) There is very limited evidence that cognitive rehabilitation may have an immediate beneficial effect on neglect. Further, there is a lack of investigations and insufficient evidence related to upper limb therapies in post-stroke subject with USN. This justifies the need for further clinical trials of cognitive rehabilitation for neglect.[^11^](#_ENREF_11) The investigations on USN using mirror therapy have either been conducted on acute subjects or underestimating the importance of motor outcome. The common neurobiological mechanism for proportional recovery rule[^33^](#_ENREF_33) both for the upper limb and USN demands the intervention of dual action. In addition to the upper limb, the USN also affects the motor and functional performance of the lower limb. However, no USN rehabilitation techniques have incorporated the lower limb aspect. The other crucial knowledge gaps in this context are: use of magnified vision for USN and use of mirror in the parasagital plane for USN. It is understood that appropriate and comprehensive intervention for USN would not only reduce the cognitive disability but also induce substantial motor and functional recovery.

1. **Novelty:**

The proposed study would be the first investigation to utilize the tasks for providing the mirror therapy among stroke subjects with USN. The meaningful tasks induce movements that appear out of an interaction between multiple brain areas to manipulate a real-world object. Such movements increase the cortical activity and may reduce greater the deficit than the movements without task.[^34^](#_ENREF_34)

Apart from the upper limb, the activity-based mirror therapy protocol[^35^](#_ENREF_35) will also be provided for the lower limb to comprehensively reduce the impact of USN. This would be the first study to incorporate the lower limbs in any USN rehabilitation study.

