**Primary objectives**

- 1. To determine the effectiveness of Task-based and Magnified mirror therapy on Unilateral Spatial Neglect (USN) among post-stroke hemiparetic subjects
  2. To determine the effectiveness of the protocol on motor recovery of the subjects

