**Inclusion Criteria:**

- Age: 20 to 80 years
- Both male & female
- First episode of unilateral stroke (as defined by WHO)
- Ischemic or hemorrhagic stroke
- 1 to 36 months after the stroke onset
- Hemiparesis (right or left) (as assessed by Fugl-Meyer assessment[^38^](#_ENREF_38) upper extremity subsection: 0 to 66)
- USN (defined as an asymmetry between the Letter cancellation task omissions in the contralesional (left) and ipsilesional (right) visual field of at least 2 letters)[^33^](#_ENREF_33)
- Normal visual abilities (with or without glasses)
- Muscle tone: Modified Ashworth scale 1 to 2

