**SPIRIT Guidelines**

|  | **STUDY PERIOD** | | | | |
| --- | --- | --- | --- | --- | --- |
|  | **Enrolment** | **Allocation** | **Intervention** | | **Follow-up** |
| **TIMEPOINT** | ***-t_1_*** | **0** | ***t_1_*** | ***t_2_*** | ***t_3_*** |
| **ENROLMENT:** |  |  |  |  |  |
| **Eligibility screen** | X |  |  |  |  |
| **Informed consent** | X |  |  |  |  |
| ***Randomization*** |  | X |  |  |  |
| **Allocation** |  | X |  |  |  |
| **INTERVENTIONS:** |  |  |  |  |  |
| ***[Task-based & Magnified Mirror Therapy]*** |  |  |  |  |  |
| ***[Control]*** |  |  |  |  |  |
| **ASSESSMENTS:** |  |  |  |  |  |
| ***[Demographic Information]*** |  | X |  |  |  |
| ***[Patient Characteristic]*** |  | X |  |  |  |
| ***[Standard Neuro-Rehab. Clinical Evaluation]*** |  | X |  |  |  |
| ***LCT*** | X |  |  | X | X |
| ***LBT*** |  |  | X | X | X |
| ***FMA*** |  |  | X | X | X |
| ***CBS*** |  |  | X | X | X |
| ***BBS*** |  |  | X | X | X |
| ***FAC*** |  |  | X | X | X |
| ***mRS*** |  |  | X | X | X |

T1 baseline assessment, T2 assessment after 8 weeks of intervention, T3 assessment after four-week follow-up (12 weeks after start of intervention). LCT = Letter Cancellation Task, LBT = Line Bisection Test, FMA = Fugl-Meyer assessment, CBS = Catherine Bergego Scale, BBS = Berg Balance Scale, FAC = Functional Ambulation Category, mRS= modified Rankin scale

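### The FMA and BBS models could also adjust for neglect severity, which is measured in every patient before allocation: a cheap precision gain of unknown size, not an error

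*Protocol*

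**What the plan says.** The Data Analysis section of the protocol specifies "A repeated-measures 2-way ANOVA (continuous data; within factor, time; between factor, group") for post-intervention and follow-up scores, and then fixes the adjustment: "The pre-intervention score will be considered as the covariate with group as the independent variable and posttest score as the dependent variable". No other covariate is named. The allocation paragraph describes blocks of 10 at 1:1 and mentions no stratification factor.

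Motor recovery is the second of two primary objectives ("To determine the effectiveness of the protocol on motor recovery of the subjects"), and FMA is listed among the primary measures.

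On prognosis, the Background states: "USN is a strong predictor of poor motor recovery and functional performances among the stroke subjects". The Rationale adds: "The presence of USN is associated with poor upper limb motor control, both at subacute and chronic stages".

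On measurement, the entry criterion is "USN (defined as an asymmetry between the Letter cancellation task omissions in the contralesional (left) and ipsilesional (right) visual field" of at least 2 letters, on a sheet with 20 targets per side. The SPIRIT schedule marks the LCT in the enrolment column, ahead of allocation. FMA, the Line Bisection Test (LBT), CBS and BBS are first marked at t1. The dummy tables for FAC and mRS show category counts with a chi-square test at each visit and no baseline term.

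**The concern.** The protocol describes neglect as prognostic for one of its two primary objectives and measures it in every patient before allocation, yet uses it neither in allocation nor in the motor model. Because the LCT is the entry test, the value should exist for all 86 patients and cannot have been affected by treatment. An entry threshold of 2 on a 20-per-side sheet allows an absolute asymmetry anywhere from 2 to 20, so severity can vary widely.

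If severity predicts later FMA beyond baseline FMA, leaving it out makes the confidence interval for the motor effect wider than it need be. A chance difference in severity between the arms would also go unadjusted. The sample size rests on the LBT alone and the protocol gives no power calculation for FMA, so precision on that objective has no stated margin.

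**Working it through.** **Figure in the plan.** The only sample-size figure concerns the LBT: mean difference 8.6, SD 10.6, α 0.05, β 0.1, 37 per group. The two-sided normal formula gives 2 × (1.960 + 1.282)² × (10.6/8.6)² = 31.9, so 32 per group (33 by t-test). The stated 37 is not reproduced; it errs on the safe side. That is a separate matter and says nothing about FMA. I use 37 per arm (74 patients) below only as the protocol's evaluable number.

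**Effect of the extra covariate.** Let R² be the share of FMA variance left after baseline FMA that enrolment LCT asymmetry explains. The documents do not give it, so it is an assumption throughout. Residual variance is multiplied by 1 − R², and the standard error by √(1 − R²).

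**Cost of the extra term.** In a single-time-point comparison with baseline adjustment, residual degrees of freedom fall from 74 − 3 = 71 to 74 − 4 = 70. Allowing for this, the standard-error ratio is √[(1 − R²) × 71/70].
- R² = 0: √(71/70) = 1.007, a standard error 0.7% larger.
- Break-even: 1 − R² = 70/71, so R² = 1.4% (partial correlation about 0.12).

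**Gain over an assumed range.** The power column assumes a true FMA effect of 0.6 SD, which is not in the documents. It uses a two-sided t-test at 0.05 and ignores the one-degree-of-freedom cost.

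| Partial R² | √(1 − R²) | SE change before df cost | SE ratio with df cost | 37/(1 − R²) per arm | Power, 37 per arm | Power, 43 per arm |
|---|---|---|---|---|---|---|
| 0% | 1.000 | none | 1.007 | 37.0 | 72.1% | 78.5% |
| 5% | 0.975 | −2.5% | 0.982 | 38.9 | 74.3% | 80.6% |
| 10% | 0.949 | −5.1% | 0.955 | 41.1 | 76.5% | 82.6% |
| 15% | 0.922 | −7.8% | 0.929 | 43.5 | 78.9% | 84.7% |

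The 43-per-arm column is shown because the plan carries the last observation forward and its dummy tables keep n = 43 at every visit. The absolute power depends on which number is used. The gain is about 2 to 7 percentage points either way.

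**Chance imbalance.** With 43 per arm, treating allocation as simple 1:1, the standardised difference in severity between arms has SD √(2/43) = 0.216. A difference of at least 0.3 SD then arises with probability about 16%. Over R² of 5% to 15% it would move the FMA comparison by 0.3 × √0.05 = 0.07 to 0.3 × √0.15 = 0.12 residual SD. The unadjusted standard error already allows for variation of this kind.

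**The case against.** The strongest objection is that the prognostic premise does not transfer to this trial. The protocol's evidence contrasts having neglect with not having it: "Post-stroke with USN exhibited poor functional outcome when compared with individuals without USN". Everyone enrolled has neglect, so that contrast does not exist here. Nothing in the protocol shows that LCT severity among neglect patients predicts FMA once baseline FMA is in the model, and baseline FMA may already carry most of the association. This stands. It is why the range must start at zero and why no gain can be promised. The wide range of eligible severity makes a link plausible; it does not establish one.

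A reader might infer that the motor comparison is biased, or that the plan is wrong. Neither follows. Adjusting for the outcome's own baseline is a valid standard analysis, and omitting a further prognostic variable does not bias a randomised comparison on average. Chance imbalance in severity is not a separate harm either.

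A reader might also extend the point to every functional outcome. The documents do not support that. CBS is itself a neglect scale, so its own baseline already carries the information. FAC and mRS are planned as chi-square tables without any covariate.

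Two further objections have some force. Covariates are often settled in the statistical analysis plan, which is not shown, and if that plan already adds this one, nothing remains to be done. But the protocol does name its covariate, so an addition is best written down before outcome data are seen. Second, time since stroke or lesion side could be argued for as well. True, but the protocol itself calls neglect a strong predictor of motor recovery and already records it before allocation.

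**Conclusion.** The point holds as an efficiency improvement for FMA, a primary measure, and for BBS. It is not an error, a contradiction or a source of bias. Its size is not documented. It runs from a standard error about 0.7% larger if severity adds nothing, through break-even at a partial R² near 1.4%, to about 2.5%, 5.1% or 7.8% smaller at 5%, 10% or 15% before the degree-of-freedom cost. These figures rest on an assumed partial R², on 37 evaluable patients per arm for the cost term, and on a simple baseline-adjusted comparison standing in for the repeated-measures model. The case for acting is that the value is already collected and the most that can be lost is small, not that a gain has been shown.

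**What to change.** In Data Analysis, add a sentence such as: *The models for FMA and BBS include the outcome's own pre-intervention score and the enrolment LCT asymmetry (absolute difference in omissions between the two sides, continuous) as covariates, whatever the observed balance between groups.*

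Use the absolute difference. The entry criteria admit right or left hemiparesis while labelling the contralesional field as left, they do not state the direction of the asymmetry, and the literature review allows for neglect on the ipsilesional side. A signed contralesional-minus-ipsilesional score could therefore be negative for some patients and rank them wrongly on severity.

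Leave the CBS model as it is, and do not extend the sentence to FAC or mRS. The cost is one sentence and one degree of freedom per model, with no new data. The downside to accept is that the gain may be close to nil.
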